### Experiment B: MIB target masking threshold for reappearance, content discrimination and confidence

**Design, stimuli, and procedure.** Experiment B repeats the design of Experiment A with the (i) inclusion of a backwards masking procedure and (ii) the elicitation of stimulus discrimination and confidence reports. Stimulus masking will be initiated when the centre of gaze crosses an invisible circular boundary around the target stimulus. Whilst in the active condition the boundary will remain stationary around the target stimulus, in the passive condition the boundary will track the stimulus as it moves (via replay) towards the centre of the screen (see Fig 2 [right]). The radius of the circular boundary will be iteratively expanded or contracted using an adaptive staircase procedure designed to identify the threshold for conscious perception of the stimulus (see Fig 2 [left]). Additionally, in experiment B instead of immediately reporting reappearance, at the completion of the trial participants will be asked whether the stimulus reappeared.

**Fig 2 pone.0328836.g002:**
[figure not shown]
Diagram of the masking boundary in experiment B. All dashed lines here are invisible to the participant. In the left panel an orange dashed circle denotes the invisible boundary in a given trial (*t*). The red dashed circle denotes a decrease in the radius for trial *t + 1* as a consequence of a report of no reappearance in trial *t*. The green dashed circle denotes an increase in the radius for trial *t + 1* as a consequence of a report of a reappearance in trial *t*. In the right panel an orange dashed circle denotes the invisible boundary in a given trial (*t*). In active trials (top) the participant moves their eyes toward the stimulus and when their gaze hits the invisible boundary centred around the target, the stimulus disappears. In passive trials (bottom) the stimulus and the invisible boundary around it are moved towards the participant’s (centrally fixated) gaze. When the invisible boundary hits the participants’ gaze the target stimulus disappears. In the right panel the black dashed arrows denote the participants gaze and the grey dashed arrow denotes how the stimulus moves over the retina.

Following each trial, if the participant reports a reappearance they will be required to discriminate the masked stimulus within a binary choice using either: the masked stimulus + a ‘no match’ option (where participants must identify that the stimulus matches the masked stimuli); or a foil drawn from the RADIATE stimulus set + a ‘no match’ option (where participants must identify that the foil does not match the masked stimulus). Half of all the choice arrays will contain the masked stimuli and half will not contain the masked stimuli. Each of the binary choices stimuli will be presented on randomly selected sides of the choice screen. Participants will make their choice by clicking on a slider using the mouse. Participants will be informed that where their cursor clicks from the centre of the screen (with the choices placed at the extremes of the slider) will be used to measure decision confidence, where clicks nearer to the ends of the slider indicate greater confidence. This choice screen is presented until the participant’s answer is confirmed with a button press.

*Training.* The training phase will be identical to that of Experiment A.

*Practice Experiment.* The practice phase will replicate that of Experiment A, with additional instruction about the stimulus discrimination task, the masking of the stimuli when making the saccades and the choice screen at the end of the trials. Participants will receive warnings if they incorrectly select foils during the stimulus discrimination task in order to encourage correct task engagement.

*Main experiment*. The main experiment follows the same general procedure outlined for Experiment A, with the additional inclusion of the backward masking, stimulus discrimination, and confidence report procedures. During active trials, participants will be cued to saccade to the target location after reporting its disappearance. When eye gaze crosses an invisible masking boundary, the stimulus will disappear. The precise radius of this boundary will be adjusted on a trial-by-trial basis (see Fig 2), such that the boundary will be expanded around the stimulus (i.e., masking is initiated earlier in the saccade) following trials in which the stimulus was reported to reappear, or the radius will be reduced around the stimulus (i.e., masking is initiated later in the saccade) following trials in which the stimulus was reported to have not reappeared. The number and length of trials will be identical with Experiment A.

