### Data collection procedures

**1. Behavioural Data.** Participants will use a key press to indicate the disappearance of the peripheral targets. A timestamp will be set when the disappearance response is given, when the cue is initiated, and when the stimuli are actively or passively foveated. This will allow precise extraction of replay gaze trajectories from the onset of fixation. In Experiment A, participants will be required to press the spacebar as soon as they become aware of the stimulus; in Experiment B, participants will be asked to give a forced binary choice after the trial to report whether stimulus reappeared. The invisible boundary that initiates the mask will be expanded if they report reappearance and contracted if they do not. If a reappearance is reported participants will be asked a subsequent question about the identity of the stimulus. The participant can choose a present identity or a ‘no match’ option. In 50% of the trials the identity shown in the trial will not match that presented in this post-trial question, allowing us to compute signal detection theoretic measures. Participant choice will also yield a confidence measure based on their click location (see Fig 3). To analyse the data we will fit linear mixed-effects models on the psychophysical awareness threshold. This will be quantified as the invisible boundary radius at which there is a 50% reappearance report rate under the model, with Active vs. Passive condition included as a predictor, potentially including and potential nuisance variables as covariates. Similar models will be fit to analyse signal detection theoretic measures of target discrimination and decision confidence.

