1)Trials in which participants fail to maintain 1.5 seconds of fixation within the allowable time period (20 seconds) are removed.2)Any values outside the screen boundary are removed and eyeblink periods are linearly interpolated based on the surrounding data points. Eye blinks are defined by pupil size > 1.5 standard deviations below or 2 standard deviations above participants average pupil size.3)Microsaccades will be quantified for each trial based on the microsaccade detection procedure defined by Engbert [42].4)Trials are epoched using a window time-locked to the cue and first fixation on a target stimulus for both eye-gaze location and pupil size. The window therefore extends before these events (to encompass the fixation, cue, and subsequent movement) and after these events. In Experiment B, the window will be extracted time-locked to the cue and the onset of the mask.5)Trials containing poor quality signals will be removed from subsequent analysis. Poor signal quality is defined as trials missing more than 30% of samples from both eyes [41]. Trials will also be rejected if the participant fails to fixate on a target stimulus or if the participant fails to maintain a central fixation in the passive condition during the period between the cue and the end of the movement sequence.

**3. Electrocardiogram.** To track physiological arousal during task performance, we will measure changes in heart period (i.e., inter-beat interval) derived from the electrocardiogram (ECG). We will acquire the ECG from a modified Einthoven lead-II configuration using either an ADInstruments PowerLab 26T device (MELBOURNE) or by a modified lead-I (clavicular) configuration using a BIOSEMI ActiveTwo EEG amplifier (JENA) and Biosemi flat active electrodes. Inter-beat intervals will be quantified as the duration between successive R-peaks (RR intervals). R-peaks will be identified using an automated QRS detection routine based on the Pan-Tompkins algorithm (e.g., [43]). Physiologically implausible inter-beat intervals (< 300 ms or > 2000 ms) will be rejected, as will any remaining intervals > 4 standard deviations from the participant’s mean. Missing intervals will be corrected via cubic-spline interpolation.

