### Operational hypotheses

The hypotheses being tested by the experiments described in this Study Protocol are as follows:

Experiment A: changes in conscious experience manifest earlier in the active than the passive condition, as measured by behavioural responses;

Experiment B: backward masking can preclude changes in conscious experience in the passive condition but not (as much) in the active condition.

These hypotheses stem from the putative role of active inference to confirm the sensory input expected following action (as described in the Introduction). Active sampling should promote faster resolution of uncertainty, engendering earlier perceptual inference. These hypotheses can be expressed in terms of the following predictions about the patterns of data we expect to observe in each experiment:

1]*Subjective report of reappearance of peripheral stimuli will occur after a shorter delay following subjective disappearance in the active vs. the passive condition of Experiment A* (see Table 1).2]*The psychophysical reappearance threshold for the radius of the masking boundary (once eye gaze is inside this invisible circular boundary the stimulus is masked) will be higher ; i.e., a larger radius in the active vs. the passive condition of Experiment B* (see Table 2).

**Table 1 pone.0328836.t001:** Predictions about the effect of active (vs. passive) sampling on target time-to-reappearance in Experiment A.

Theory	Decrease	No change	Increase	Confidence
IIT	X	X		Low
NREP	X	X		Medium
AI	X			High

**Table 2 pone.0328836.t002:** Predictions about the effect of active (vs. passive) sampling on mask onset boundary distance in Experiment B.

Theory	Decrease	No change	Increase	Confidence
IIT		X	X	Low
NREP		X	X	Medium
AI			X	High

Each of the other theories considered in the adversarial collaboration, IIT and NREP, offer different predictions to these, which also differ in their degree of confidence:

IIT is consistent with both manipulations (active or passive target sampling) quickly breaking suppression, by changing visual cortex state. Motor involvement (active) may be enough to tip the balance towards breaking suppression more easily, for a small difference in time to reappearance and/or masking boundary. Thus, for Experiment A (see Table 1), IIT predicts either decrease or no change, with low confidence; for Experiment B (see Table 2), IIT predicts either increase or no change, with low confidence.

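### Experiment B compares programmed mask radii, but the article does not secure that one radius means the same effective removal distance in active and passive trials; unmatched delay would push the active threshold in the predicted direction

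*Protocol article*

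**What the plan says.** The Behavioural Data item under Data collection procedures fixes the Experiment B outcome as "the invisible boundary radius at which there is a 50% reappearance report rate under the model", modelled with condition as predictor. Operational hypotheses states the predicted result as "a larger radius in the active vs. the passive condition of Experiment B", and Table 2 enters it as AI-C's high-confidence prediction.

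The two conditions reach the boundary differently. In active trials the boundary stands still around the target and the eye moves into it: "When eye gaze crosses an invisible masking boundary, the stimulus will disappear" (Experiment B, Main experiment). In passive trials the participant holds fixation and "in the passive condition the boundary will track the stimulus as it moves (via replay) towards the centre of the screen". The Fig 2 caption words the passive trigger as gaze contact as well: "When the invisible boundary hits the participants’ gaze the target stimulus disappears".

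The Aim section says that replay makes visual stimulation identical across conditions, and Current study says the same of visual input and retinal activation. The eye-tracking analysis steps already refer to a mask-onset event: "In Experiment B, the window will be extracted time-locked to the cue and the onset of the mask". That event is used to cut epochs, not to define the threshold.

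**The concern.** The programmed radius is an instruction to the display. What reaches the participant is how far the target was from the centre of gaze when it actually left the screen. The two agree only if removal is instantaneous.

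In active trials the crossing occurs during the saccade. Between the crossing and the first frame without the target, the gaze sample has to be processed and the screen redrawn, and the eye keeps closing on the target meanwhile. In passive trials tracker delay hardly matters because gaze is stationary; only a lag in redrawing the moving target would bring removal inward.

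If active removal is effectively later, active participants see the target nearer the fovea at the same programmed radius. They report more reappearances, the staircase enlarges the boundary, and the fitted active threshold rises. That is the result the protocol would read as support for AI-C. At stake is whether an active-passive difference in radius can be attributed to perception and not to equipment timing.

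**Working it through.** **Inputs from the article.** Target at 9 degrees from fixation (Experiment A, design, carried into Experiment B); gaze sampled at 1000 Hz; 55 participants for at least 80% power at partial eta squared 0.13. It states no end-to-end delay, refresh rate, alpha or staircase radii.

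**Assumptions.** Minimum-jerk saccade of 35, 45 or 60 ms; removal delay of 2 to 30 ms; refresh rates of 60 to 240 Hz; two-sided alpha of 0.05; SD of the paired difference in thresholds of 1 to 4 degrees.

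**1. The plan's own figure.** With two within-subject levels, f² = 0.13/0.87 = 0.149, so f = 0.387. The F test on (1, n − 1) degrees of freedom with noncentrality n·f² has power 0.796 at n = 54 and 0.804 at n = 55. The stated 55 reproduces. The sample size is not in dispute; the same formula is used in step 4.

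**2. Excess in the programmed active radius, no passive lag.** Eye position is pos(t) = 9(10τ³ − 15τ⁴ + 6τ⁵), with τ = t/D and D the saccade duration. To be removed at effective distance r, the target must be triggered L ms earlier, so the programmed radius must be 9 − pos(t_r − L), where t_r is the time at which the remaining distance is r.

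Example: D = 45 ms, r = 4 degrees, L = 5 ms. The eye is 4 degrees away at τ ≈ 0.530, or 23.8 ms. Five ms earlier τ ≈ 0.418 and the remaining distance is 5.85 degrees. The excess is 5.85 − 4 = 1.85 degrees.

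Over D = 35, 45 and 60 ms and r = 2, 4 and 6 degrees:

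| Assumed delay | Excess in programmed active radius |
|---|---|
| 2 ms | 0.48 to 0.96 degrees |
| 5 ms | 1.21 to 2.35 degrees |
| 10 ms | 2.14 to 4.56 degrees |
| 20 ms | 2.97 to 6.95 degrees where a match exists |

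At 20 ms, 3 of the 9 combinations have no matching radius within the 9-degree path; at 30 ms, 7 of 9 have none.

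**3. Allowing the passive condition to lag.** A frame-by-frame simulation (45 ms saccade; 60, 120, 144 and 240 Hz; tracker delay of 2, 5 or 10 ms; programmed radii of 4 and 6 degrees) compares gaze-to-target distance at active removal with the last drawn target distance in passive trials. This is a gap in effective distance at a fixed radius, not the excess of step 2.

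- No passive lag: 6.69 − 4.50 = 2.2 degrees (240 Hz, 2 ms, radius 6) up to 8.02 − 0.69 = 7.3 degrees (60 Hz, 10 ms, radius 6). Part of this arises because the last passive frame is drawn outside the boundary.
- One frame of passive lag: 1.55 − 1.12 = 0.4 degrees (60 Hz, 2 ms, radius 4) up to 5.24 − 1.76 = 3.5 degrees (240 Hz, 10 ms, radius 6).

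Active removal was nearer the fovea in every case run. Longer passive lags were not run.

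**4. Consequence for the test.** With no true effect, a bias b and SD s give noncentrality 55(b/s)². The false-positive rate reaches about 80% at b = 0.387·s: 0.39, 0.77, 1.16 and 1.55 degrees for SDs of 1, 2, 3 and 4. A 1-degree bias gives 95% if the SD is 2 and 45% if it is 4.

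**The case against.** A reader might infer that removal lags only in the active condition and that the active staircase must therefore settle at a larger radius. The article does not support that. The Experiment B design paragraph gives one gaze-crossing trigger for the whole experiment, and the Fig 2 caption describes passive removal as the boundary meeting the participant's gaze. Passive targets follow a replay of a recorded saccade, so any redraw delay lets them travel inward too. Equal delays would cancel, and a passive delay longer than the active one could reverse the sign. That part of the objection stands: the bias is conditional.

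A reader might also multiply a long delay by a high gaze speed, for example 20 ms × 400 degrees/s = 8 degrees. That treats peak speed as constant over almost the whole 9-degree path, and an inward offset cannot exceed the programmed radius. It is not a usable estimate.

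The objection also notes that refresh rate, latency and trigger code are details an article commonly leaves to fuller documents, and that this one cites a preregistration and promises its code. That is fair, and their absence is not the point. What remains is the endpoint, which the article does define, on the programmed radius, alongside a statement that stimulation is identical across conditions. Tracker delay is intrinsically costlier when the eye is moving than when it is still, and a one-frame passive lag reduced the gap without removing it.

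**Conclusion.** The point holds as a design risk with a likely direction, not as a demonstrated bias. The endpoint is a nominal setting, and the article does not show that it corresponds to the same effective removal distance in both conditions. Unless delays are matched, the active threshold tends to be biased upward, as Table 2 predicts for AI-C.

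The size is not in the documents. The range of roughly 0.5 to 4.6 degrees rests on assumed delays of 2 to 10 ms, an assumed saccade profile and no passive lag. Even the lower part of that range could matter for the test if the paired-difference SD is about 1 to 2 degrees, which is also assumed. Matched delays, or a correction in a document not shown, would remove the concern. The change is worth making because it is cheap and replaces the nominal setting with the quantity the hypothesis is about.

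**What to change.** Define the primary Experiment B threshold on the gaze-to-target distance at the first target-absent frame in both conditions, using the position at which the target was last drawn. Fit the 50% report function and the active-passive contrast to that distance at trial level. Report the programmed radius only as the staircase setting.

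The inputs are the 1000 Hz gaze record and the mask-onset time that the eye-tracking analysis already uses. Confirm that this time marks the physical screen change and not the trigger; the timestamps listed under Behavioural Data do not include it. If it marks the trigger, add the display lag measured at each site. Data collection is already underway according to Status and timeline, so this should be checked now.

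No new trials are needed and the 55 participants stand. With distance measured at the physical screen change, the lag-induced difference falls to zero and the false-positive rate from this source returns to the nominal 5%. The costs are a somewhat noisier fit, because actual distances scatter around the staircase value, and one limit: re-coding cannot rescue trials in which the active staircase had reached its maximum.

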### Data collection procedures

**1. Behavioural Data.** Participants will use a key press to indicate the disappearance of the peripheral targets. A timestamp will be set when the disappearance response is given, when the cue is initiated, and when the stimuli are actively or passively foveated. This will allow precise extraction of replay gaze trajectories from the onset of fixation. In Experiment A, participants will be required to press the spacebar as soon as they become aware of the stimulus; in Experiment B, participants will be asked to give a forced binary choice after the trial to report whether stimulus reappeared. The invisible boundary that initiates the mask will be expanded if they report reappearance and contracted if they do not. If a reappearance is reported participants will be asked a subsequent question about the identity of the stimulus. The participant can choose a present identity or a ‘no match’ option. In 50% of the trials the identity shown in the trial will not match that presented in this post-trial question, allowing us to compute signal detection theoretic measures. Participant choice will also yield a confidence measure based on their click location (see Fig 3). To analyse the data we will fit linear mixed-effects models on the psychophysical awareness threshold. This will be quantified as the invisible boundary radius at which there is a 50% reappearance report rate under the model, with Active vs. Passive condition included as a predictor, potentially including and potential nuisance variables as covariates. Similar models will be fit to analyse signal detection theoretic measures of target discrimination and decision confidence.

**Fig 3 pone.0328836.g003:**
[figure not shown]
An example resolved LMM analysis decision tree for experiment A & B. Here solid lines denote variables to be considered and grey boxes (dotted lines) denote decision criteria. Note: 1) Crossed out options are for example only, all options are available in real analysis tree. 2) For display purposes only included variables are written in full but variable selection at each level includes the same forks. 3) The third level criteria uses ascending steps to decide model variable inclusion. 4) Top of the tree denotes the basic model.

Trials will be rejected if:

1)any button press response is made < 3 seconds following the start of the trial2)time to reappearance is reported < 250 ms following the cue.3)time to reappearance is reported > 1 second following the cue.

**2. Eye-tracking.** Binocular gaze and pupillary response data for the experiment will be sampled at a frequency of 1000 Hz using a desk mounted SR Research Eyelink 1000 system (35 mm lens). Testing will be conducted in a sound attenuated room and display luminance will be matched across recording sites (Melbourne and Jena) using luminance measures taken from the four screen quadrants, taking into account room lighting. Participants will be seated with their head stabilised on a chin rest mounted 105.3 cm from the stimulus presentation screen and ~55 cm from the eye-tracking camera to the eye. At the start of the experiment a nine-point calibration and nine-point validation will be conducted. An additional validation will be performed at the start of each block. If any inter-block validation is not considered ‘good’ (worst point error < 1.5°, average error < 1.0°), the initial calibration and block validation will be repeated.

***Passive condition, eye-movement replay.*** The replay data processing must be completed within the inter-block period and has therefore been kept relatively streamlined to prevent additional computation time:

1)Replay periods are epoched using a window extending from the initialization of the cue to the first fixation on the target stimulus.2)Any values outside of the boundaries of the screen are removed, and eyeblink periods must be linearly interpolated between points in order to maintain a smooth replay. Any datapoint more than 1.5° of visual angle away from the linear path from fixation to target will not be considered in the replay. Any datapoint more than 1.5° away from the previous data point is considered an error and will not be considered in the replay.3)Any trials containing poor signals (i.e., missing more than 20% of sample points in both eyes; [41]) will not be selected for replay. For replays that meet this standard all non-included samples will be linearly interpolated. To ensure equal numbers of active and passive trials, active trials may be used in replays additional times after running through all available replays. The replay path corresponding with the target stimuli will be used for replay if available, but the path trajectory will be transformed across randomly selected polar angles.

***Analysis.*** The following pre-processing steps describe the post-experiment analysis of eye tracking data for use in trial validation, eye-blink, microsaccade and pupillometry measures:

1)Trials in which participants fail to maintain 1.5 seconds of fixation within the allowable time period (20 seconds) are removed.2)Any values outside the screen boundary are removed and eyeblink periods are linearly interpolated based on the surrounding data points. Eye blinks are defined by pupil size > 1.5 standard deviations below or 2 standard deviations above participants average pupil size.3)Microsaccades will be quantified for each trial based on the microsaccade detection procedure defined by Engbert [42].4)Trials are epoched using a window time-locked to the cue and first fixation on a target stimulus for both eye-gaze location and pupil size. The window therefore extends before these events (to encompass the fixation, cue, and subsequent movement) and after these events. In Experiment B, the window will be extracted time-locked to the cue and the onset of the mask.5)Trials containing poor quality signals will be removed from subsequent analysis. Poor signal quality is defined as trials missing more than 30% of samples from both eyes [41]. Trials will also be rejected if the participant fails to fixate on a target stimulus or if the participant fails to maintain a central fixation in the passive condition during the period between the cue and the end of the movement sequence.

**3. Electrocardiogram.** To track physiological arousal during task performance, we will measure changes in heart period (i.e., inter-beat interval) derived from the electrocardiogram (ECG). We will acquire the ECG from a modified Einthoven lead-II configuration using either an ADInstruments PowerLab 26T device (MELBOURNE) or by a modified lead-I (clavicular) configuration using a BIOSEMI ActiveTwo EEG amplifier (JENA) and Biosemi flat active electrodes. Inter-beat intervals will be quantified as the duration between successive R-peaks (RR intervals). R-peaks will be identified using an automated QRS detection routine based on the Pan-Tompkins algorithm (e.g., [43]). Physiologically implausible inter-beat intervals (< 300 ms or > 2000 ms) will be rejected, as will any remaining intervals > 4 standard deviations from the participant’s mean. Missing intervals will be corrected via cubic-spline interpolation.

